#### Secondary Outcomes

We will investigate the differences in model performance across various conditions to propose recommendations for interpreting the model. Accuracy, sensitivity, and specificity will be evaluated using a mixed-effects model with fixed effects for patients and random effects for the type of condition (ST, DCT, and DMT) and medication state (“on” and “off”).

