Regardless of the wearable sensors used or the freezing protocol, the accuracy of detection is sensitive to the type of algorithm [9,11,12,23]. Yet, the algorithms used to detect FoG episodes are controversial, especially for real-time detection. The threshold method provides a straightforward approach to the implementation and interpretation of algorithms. In this context, the freezing index—defined as the ratio between the power bands of freezing (3-8 Hz) and locomotion (0.5-3 Hz)—is the most commonly used feature in threshold-based algorithms [9,11,12,23]. This single feature accurately detects many FoG episodes (sensitivity: 84.3%; specificity: 78.4% [24]), but detection fails when no motion is observed and voluntary stops may be mistakenly classified as FoG [17]. Adding multiple indices can enhance algorithm performance, but it also increases complexity and the difficulty of tuning thresholds [25,26]. To address these limitations, machine learning (ML) algorithms have been developed to improve FoG detection performance. Indeed, ML algorithms could better fit the model to increase the accuracy of the models; this is a subfield of artificial intelligence that gives an algorithm the ability to learn without being explicitly programmed [12]. Among the various ML algorithms, support vector machine, multilayer perceptron, and ensemble classifiers (eg, random forest or AdaBoost) have proven to be the most efficient. Determining the best ML algorithm is challenging due to the highly heterogeneous nature of the training data. A limitation of ML algorithms is that training the model and processing the data can require high computational cost. Fortunately, advances in computer technology now offer the possibility of early or real-time detection with ML models [12].

The primary objective is to assess the accuracy of the optimal combination of wearable sensors for detecting FoG episodes in patients with PD. The secondary objectives of this study include measuring the specificity, sensitivity, positive predictive value (PPV), and negative predictive value (NPV) of the optimal combination of wearable sensors for detecting FoG episodes. Regarding the setup, we also aim to compare its performance (accuracy, sensitivity, specificity, PPV, and NPV) across various clinical and medical conditions.

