## Methods

### Study Design and Participants

This study is a single-center, prospective cohort trial (DetectFoG) involving patients with PD with FoG at the University Hospital of Rennes. Patients will be recruited from the neurology department of University Hospital of Rennes during their visit to the neurologist. This study aims to include a total of 18 patients. To mitigate potential issues such as withdrawal of consent, absence of FoG during neurologist annotation, loss of follow-up (failure to attend the second visit), or inability to complete the required number of passages (fewer than 6), initially, 20 patients will be enrolled. Participants experiencing any of these issues will be excluded from the study.

Inclusion criteria will include patients older than 18 years diagnosed with PD according to the UK Brain Bank criteria. Patients must self-report as freezers, scoring between 1 and 3 on question 13 of the Movement Disorder Society-Unified Parkinson’s Disease Rating Scale (MDS-UPDRS) II [27], and be capable of walking 30 m without assistance to complete the freezing-provoking path. Exclusion criteria will apply to patients scoring less than 20 out of 30 on the Montreal Cognitive Assessment [28] who are unable to give informed consent and those with neurological, orthopedic, or rheumatic comorbidities that could impact gait and ability.

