**Figure 1 figure1:**
[figure not shown]
Timeline of study. IMU: inertial measurement unit.

For organizational purposes, the first visit (inclusion visit) will occur during the “on” phase of levodopa medication, while the second visit (follow-up visit) will be during the “off” phase. During the “on” phase, patients will be assessed when oral treatment maximally improves dopa-sensitive PD symptoms (best “on” state, typically 1-2 hours after ingestion). This state will be determined based on patients’ subjective assessment, similar to their daily motor self-assessments (home diaries), which has been established as reliable in various studies [29-31]. Assessment during the “off” phase will occur after 12 hours without treatment, preferably in the morning before the first levodopa dose.

During each visit, participants will walk on a freezing-provoking path at a comfortable speed under 3 different clinical conditions (single task [ST], dual cognitive task [DCT], and dual motor task [DMT]). The Pardoel freezing-provoking path, known to induce FoG episodes [32], includes standing up, walking with a slalom (left and right turns), navigating a narrow passage with a 180° turn, and returning straight, with 2 designated stops—one chosen by the patient and another in front of a chair (Figure 2).

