**Figure 2 figure2:**
[figure not shown]
Freezing-inducing path (adapted from Pardoel et al [32], which is published under Creative Commons Attribution 4.0 International License [33]).

Participants will undergo testing under different dual-task conditions, which are recognized for promoting FoG episodes [32]. The DMT involves walking with a ball on a tray within a drawn circle, keeping the ball centered. The DCT requires participants to generate as many words as possible starting with a specified letter. Each participant will complete a maximum of 6 blocks, with each block consisting of the 3 conditions (ST, DCT, and DMT), resulting in a total of 18 trials (6 blocks × 3 conditions per block). The sequence of conditions within each block will be randomized to mitigate any order effects. This protocol accommodates varying endurance levels among patients; some may complete each block quickly with few or no FoG episodes, while others may take longer due to frequent tremors that consume energy. This flexible approach ensures that the study is comprehensive and respects each patient’s physical limitations. However, participants who complete fewer than 2 blocks (6 trials) will be excluded from the analysis to ensure adequate data collection.

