#### Model Validation

The model validation will use the leave-one-subject-out (LOSO) cross-validation technique to assess its performance across participants and accommodate the considerable variability between participants. While some studies [20,42] advocate for the leave-one-freezer-out (LOFO) cross-validation technique to avoid overrepresentation of patients without FoG in training and validation sets, our study focuses on participants who have experienced at least 1 episode of FoG during their initial visit. Consequently, each patient will have FoG episodes, making the LOSO approach more suitable for our validation process.

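### The model for comparing detection performance across conditions has no patient-by-condition terms and treats conditions as random, so it estimates no average on/off or task difference and could understate the error of one

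*Protocol article*

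**What the plan says.** The secondary objective at the end of the Introduction is to "compare its performance (accuracy, sensitivity, specificity, PPV, and NPV) across various clinical and medical conditions". Under Statistical Analysis, Secondary Outcomes, the purpose is given as: "We will investigate the differences in model performance across various conditions to propose recommendations for interpreting the model". Accuracy, sensitivity and specificity are then to be analysed with a "mixed-effects model with fixed effects for patients and random effects for the type of condition (ST, DCT, and DMT) and medication state". These three terms are all that the sentence names. It gives no null hypothesis, contrast, significance level or row level (one row per trial, or one value per patient and condition).

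The design facts that matter:

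- Sample: "This study aims to include a total of 18 patients", for which "initially, 20 patients will be enrolled".
- Each medication state is observed at one visit, in a fixed order: "the first visit (inclusion visit) will occur during the “on” phase of levodopa medication, while the second visit (follow-up visit) will be during the “off”".
- Trials: "Each participant will complete a maximum of 6 blocks, with each block consisting of the 3 conditions". The Protocol section puts the total at 18 trials without saying whether that is per visit or overall, and excludes patients with fewer than 2 blocks.

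**The concern.** A comparison of conditions that is meant to support recommendations is a statement about the average shift across patients. Two features of the model work against it.

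First, the roles are reversed. Medication state (2 levels) and task (3 levels) are the conditions of interest, but they are declared random. The patients, who are the sample, are declared fixed. The model then returns variances for state and task, not an average on/off or task difference.

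Second, even with the roles put right, nothing lets the on/off or task shift differ between patients. All such variation goes into a pooled residual that treats rows as independent. The on/off contrast rests on 18 within-patient differences (17 df), whereas the additive model works with the residual df of all rows. A chance imbalance among 18 individuals could then be reported as a general effect of medication or dual-tasking.

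The two faults are separate. In a balanced layout the additive F ratio for medication is MS(medication)/MS(residual) whichever terms are called random, so exchanging the roles alone leaves the second fault in place.

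**Working it through.** The article gives no figure to reproduce for this comparison: no alpha, SD, effect size or power. The check is therefore conditional.

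**Inputs from the article:** N = 18 patients, 2 states, 3 tasks. Rows per cell, b: 1 if each patient-by-state-by-task cell is one value; 3 if 18 trials are done in all (18/6 cells); 6 if 18 are done per visit (36/6 cells).

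**Assumed:** alpha 5%; no average effect; residual SD 1; patient-by-state and patient-by-task effects each with SD tau per condition level, tau from 0 to 1; balanced data.

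**Expected mean squares with no average effect**

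- Medication: 1 + 3b·tau²
- Task: 1 + 2b·tau²
- Residual df of the additive model: 6bN − N − 3, which is 87, 303 and 627 for b = 1, 3 and 6
- Pooled residual: 1 + (17·3b + 34·2b)·tau²/df = 1 + 119b·tau²/df

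The additive F statistic behaves approximately as the inflation ratio (effect mean square over pooled residual) times a central F. The rejection rate is therefore close to P(F > critical value/ratio).

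**On/off test, additive model**

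| b | tau | Medication MS | Residual MS | Ratio | Rejection |
|---|---|---|---|---|---|
| 1 | 0.5 | 1.75 | 1.342 | 1.30 | 8.5% |
| 1 | 1 | 4 | 2.368 | 1.69 | 13% |
| 3 | 0.5 | 3.25 | 1.295 | 2.51 | 21–22% |
| 3 | 1 | 10 | 2.178 | 4.59 | 36% |
| 6 | 0.5 | 5.5 | 1.285 | 4.28 | 34% |
| 6 | 1 | 19 | 2.139 | 8.88 | 51% |

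Repeated simulations of the same layout agree within Monte Carlo error: about 7–14%, 21–37% and 35–51% for b = 1, 3 and 6. At tau = 0.25 the rates are about 6%, 10% and 16%. At tau = 0 they are 5% throughout.

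**Task test, additive model.** The same formulas give about 7–9% (b = 1), 21–39% (b = 3) and 38–61% (b = 6) for tau 0.5 to 1.

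**With patient-level error terms.** Testing medication against patient-by-medication (1 and 17 df) and task against patient-by-task (2 and 34 df) gives between 4.5% and 5.6% in every setting.

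**The model exactly as written.** Here the nearest test is a likelihood-ratio test that the medication variance is zero (cut-off 2.706). With no patient-by-medication variation it rejects about 2%, so it is conservative. With the SD of the on/off difference at 0.5 to 1 residual SD (tau = that value/√2, or 0.35 to 0.71), it rejects 4–10%, 10–27% and 18–41% for b = 1, 3 and 6. The estimate itself carries little information. A random medication SD rests on 1 df, so its 95% limits run from about √(1/5.02) = 0.45 to about 32 times the estimate. For task (2 df) they run from about 0.52 to 6.3 times.

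**The case against.** The strongest case against runs as follows.

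- **No null is written.** A reader might infer that the plan states a null of no average difference and tests it at the wrong level. It does not. The null is implied by the objective, and no test is described. The point is what the named model could support.
- **Response variation is assumed.** A reader might take the Model Validation remark about the need to "accommodate the considerable variability between participants" as the article's admission that patients differ in their on/off or task shift. That sentence justifies leave-one-subject-out validation and concerns variability in general; differences in level are absorbed by the patient term. The article gives no figure for variation in response. Some is plausible, since each state is seen at one visit and sensors are positioned by hand, so day and placement effects are shared by all trials of a visit. Its size is unknown.
- **The largest rates need the least certain design.** Rates of 35% and above for on/off at tau 0.5 need six trial rows per cell. The Discussion says each patient completes 18 passages, which fits three per cell, and 6 blocks is a maximum.
- **Trial rows may not be used.** Sensitivity is undefined in a trial with no FoG window, so one value per cell is at least as plausible, and inflation is then modest.
- **The sentence may be shorthand** for condition effects that vary within patient, which would supply the missing terms. That is not its plain reading, because patients are declared fixed and no grouping by patient is named.
- **Detail may sit in an unseen analysis plan.** That would excuse silence on row level or degrees of freedom. It does not excuse a model that the article does specify and whose roles are reversed.

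The first four limit the size of the claim. None removes it.

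**Conclusion.** The point holds conditionally. It is certain from the text that the named model is additive, contains no patient-by-condition term, and, with conditions random and patients fixed, estimates no average on/off or task difference. That does not serve the comparison it is meant to deliver.

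The inflation of a test of an average difference is conditional on patients differing in their response, and its size depends on the row level: modest with one value per cell, serious with three or six trial rows per cell, and absent if responses do not vary. The calculations assume balanced data, whereas patients may complete anywhere from 2 to 6 blocks, so the rates are a guide and not a forecast. A flat claim that the plan rejects far too often would go beyond the documents. These are secondary analyses and the correction is cheap, so it should be made before analysis; the primary outcome is not affected.

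**What to change.** In the Secondary Outcomes section:

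1. Make task and medication state fixed effects and patient a random effect.
2. Add random patient-by-medication and patient-by-task terms, with Kenward-Roger or Satterthwaite degrees of freedom.
3. State whether a row is a trial or a patient-by-condition value.
4. Name the fallback if the model does not converge: one value per patient per state with a paired comparison (17 df for 18 patients), and for task a repeated-measures test against patient-by-task variation.

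Steps 1 and 2 belong together. Adding patient slopes while leaving the conditions random still gives no average contrast, and exchanging the roles alone leaves the error term too small.

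The change takes a few lines of text and no new data. The price is wider intervals and lower nominal power for condition effects.

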Despite numerous studies and literature reviews on the use of these wearable sensors for FoG detection, there is as yet no consensus in the literature on the optimal methodology for their use. It is likely that this discrepancy stems from the inherent variability in the protocols used. Indeed, there is considerable heterogeneity in the protocols for triggering [11] (medical condition: “on” or “off” levodopa treatment; freezing-provoking path; and dual-task conditions). In fact, there are few studies that directly compare FoG episodes in “on” and “off” conditions with small cohorts and a low number of participants [11,12,14]. Furthermore, many locations including feet, shin or ankle, thigh, and pelvis have been investigated [15]. The use of multiple sensors provides a more detailed and holistic view of the patient’s movements, enabling the capture of subtle changes that may not be detectable with a single sensor [15]. An IMU is cost-effective and straightforward to wear, rendering it suitable for both laboratory evaluation and daily use. Even if patients prefer to wear sensors solely at the wrist, such as a stopwatch, or conceal them beneath clothing at the ankle or on a belt (lower back), as demonstrated by O’Day et al [15], the placement of sensors on multiple body parts could enhance the robustness of FoG detection across various walking tasks and different FoG subtypes. Furthermore, examining FoG under dual-task conditions provides a more comprehensive understanding of how cognitive load impacts freezing episodes, which only a few studies have addressed [16-20]. Finally, several other variables may confound the study, including the wide age range of cohorts (aged 7-118 years) and the diverse range of FoG episodes (50-1110) [21-23]. Therefore, this study is innovative as it stands out for its ability to replicate findings across various conditions, particularly the medical condition. Furthermore, it explores the effects of dual-task scenarios and optimal sensor placement in a larger cohort than those found in the literature, significantly enhancing our understanding of the underlying mechanisms. These multiple dimensions provide a more nuanced and robust perspective, allowing for better generalization of the results and improving practical applications in medical settings.

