### Protocol

After verifying the inclusion and exclusion criteria, the neurologist will notify the principal investigator (KJ). The principal investigator will then contact the patients to provide comprehensive and understandable information about the study’s objectives, as well as their right to refuse participation or withdraw at any time. If the patients consent and sign the consent form, they will participate in 2 visits separated by 2 weeks (±7 days), encompassing both “on” and “off” phases of levodopa treatment (Figure 1).

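### The mixed model for the secondary comparison has its fixed and random roles reversed, so as written it contains no task or on/off effect with an estimate and confidence interval.

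*Protocol article*

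**What the plan says.** The objectives at the end of the Introduction say of the chosen sensor setup that "we also aim to compare its performance (accuracy, sensitivity, specificity, PPV, and NPV) across various clinical and medical conditions". The Secondary Outcomes paragraph under Statistical Analysis repeats the purpose: "We will investigate the differences in model performance across various conditions to propose recommendations for interpreting the model". The next sentence gives the method. Accuracy, sensitivity and specificity are to be evaluated with a "mixed-effects model with fixed effects for patients and random effects for the type of condition (ST, DCT, and DMT) and medication state". The article specifies no other analysis for comparing conditions, and nothing elsewhere corrects this one.

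The surrounding design is clear:

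- **Patients:** "This study aims to include a total of 18 patients" (Study Design and Participants).
- **Conditions:** every patient is to walk under three tasks (ST, DCT, DMT) at each of two visits. The first visit is always in the on state and the second in the off state (Protocol section, text after Figure 1).
- **Variation between patients:** Model Validation chooses leave-one-subject-out validation to "assess its performance across participants and accommodate the considerable variability between participants".
- **Intended reach:** the Introduction presents the design as "allowing for better generalization of the results and improving practical applications in medical settings".

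**The concern.** A mixed model estimates differences between the levels of its fixed factors and summarises its random factors by a variance. Fixed factors are levels chosen for their own sake. Random factors are samples from a larger population. Here, on versus off and ST versus DCT versus DMT are the chosen levels whose differences are the question, and patients are the sample. The specification assigns them the other way round.

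An analyst who follows the text would obtain 17 differences between individual patients, which no objective asks for, and no coefficient for medication or task. The text also names no patient-by-condition term. If the on/off change in performance differs between patients, nothing in the model carries that variation into the uncertainty of a comparison. The recommendations that the paragraph promises would then rest on a model that does not supply the comparison behind them.

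**Working it through.** The article gives no effect size, standard deviation or alpha for this analysis, so there is no figure of its own to reproduce. The check has four steps. The first rests on the documents alone; the third and fourth use stated assumptions.

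**1. Count the parameters.** Inputs: 18 patients, 3 tasks, 2 medication states, one value per patient, task and state (18 × 3 × 2 = 108 values).

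| | As written | Roles corrected |
|---|---|---|
| Fixed: patient contrasts | 18 − 1 = 17 | none |
| Fixed: task contrasts | 0 | 3 − 1 = 2 |
| Fixed: medication contrasts | 0 | 2 − 1 = 1 |
| Fixed: task-by-medication contrasts | 0 | 2 × 1 = 2 |
| Task and medication as variance components | 2 | none |

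Fitting the written model to one simulated data set of this shape confirmed the count: an intercept, 17 patient coefficients, a medication variance and a task variance.

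**2. What the variance components can say.** A 95% interval for a standard deviation on df degrees of freedom runs from √(df/χ²₀.₉₇₅) to √(df/χ²₀.₀₂₅) times the estimate.

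- Medication, 1 df: √(1/5.024) = 0.45 to √(1/0.000982) = 31.9 times.
- Task, 2 df: √(2/7.378) = 0.52 to √(2/0.0506) = 6.3 times.

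These intervals treat the level effects as observed without error. They describe the variance component, not the precision of an on/off or task difference.

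**3. Shrunken predictions.** Assumed standard deviations on the proportion scale: patient 0.08, patient-by-medication 0.06, patient-by-task 0.04, residual 0.05. There were 4,000 simulated trials per true off-minus-on difference, analysed with the balanced analysis-of-variance equivalent.

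| True difference | Mean fixed contrast | Mean shrunken prediction | Medication variance estimated as zero |
|---|---|---|---|
| 0 | −0.0005 | −0.0004 | 48% |
| −0.03 | −0.0302 | −0.0247 | 22% |
| −0.06 | −0.0601 | −0.0559 | 2% |
| −0.10 | −0.1001 | −0.0978 | 0% |

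The predictions exist but are pulled towards zero, and when the variance is estimated as zero the predicted difference is zero too.

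**4. Omitted patient-by-condition variation.** At a true difference of 0, testing medication against the pooled residual rejected in 19.6% of simulations at nominal 5%. A paired t test on patient means rejected in 5.4%. Arithmetic agrees with the first figure:

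- Expected mean square for medication: 0.05² + 3 × 0.06² = 0.0133.
- Residual df in the additive model: 108 − 18 − 2 − 1 = 87. These comprise 17 patient-by-medication, 34 patient-by-task, and 36 for the rest (2 task-by-medication, 34 pure residual).
- Expected residual mean square: (17 × 0.0133 + 34 × (0.05² + 2 × 0.04²) + 36 × 0.05²)/87 = (0.2261 + 0.1938 + 0.0900)/87 = 0.00586.
- Ratio: 0.0133/0.00586 = 2.27. The standard error is too small by a factor of √2.27 = 1.51, and 2 × [1 − Φ(1.96/1.51)] ≈ 0.19.

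This inflation comes from the missing patient-by-medication term. Swapping the roles with only a random patient intercept would not remove it, which is why the fix names that term.

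**The case against.** The strongest case against is that the two terms were probably swapped in drafting, that the analysis is secondary, and that any statistician would notice. That may be so. But this is the article's only specification, it states a model rather than leaving one open, and it conflicts with the sentence before it.

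Other parts of the objection stand and limit the point. A reader might infer four stronger things that the documents do not support:

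- **That the model can say nothing about condition differences.** It can: shrunken predictions of each level can be extracted. What it lacks is a fixed contrast with an estimate and confidence interval.
- **That 17 degrees of freedom are wasted on patients, or that fixed patient effects alone tie inference to these 18 people.** In a balanced within-patient design, once condition is fixed, fixed patients and a random patient intercept give the same contrast and standard error. In one simulated 18 × 3 × 2 set both gave −0.03624 (SE 0.00952). The limit on generalising comes from leaving out patient-by-condition variation.
- **That the wide variance intervals measure how poorly on versus off would be estimated.** They do not (step 2).
- **That on-state single-task cells are likely to hold no freezing.** No rates by cell are given. Model Validation says only that participants have at least one episode at the initial visit, and Video Recording and Window Labeling counts a window as freezing only if all 2 seconds are. Empty cells are therefore possible, but the article does not show which.

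A ready remedy, a plain binomial model on window counts, also meets a fair objection. Windows of 2 seconds shifted by 0.4 seconds overlap by 80% and are not independent trials. If correlation simply follows overlap (an assumption: 0.8, 0.6, 0.4, 0.2 at lags 1 to 4), the design effect is 1 + 2 × 2.0 = 5. Standard errors would be too small by √5 = 2.24, and a nominal 5% test would reject about 38% of the time where binomial error dominates. Nor does such a model rescue cells with no freezing windows: with TP + FN = 0 they add nothing to the likelihood.

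**Conclusion.** The point holds. The written model reverses the roles of patients and conditions. It contains no task or on/off effect with a confidence interval and no term for variation in condition effects between patients. It therefore does not deliver the comparison that the Introduction and the Secondary Outcomes paragraph both set as an aim.

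The structural part (0 condition coefficients as written, against 2 for task, 1 for medication and 2 for their interaction once corrected) follows from the text and rests on no assumption. The simulated figures (19.6% against 5.4% false positives, a mean prediction of −0.0247 for a true −0.03) depend on the assumed standard deviations and illustrate direction rather than size.

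The defect is confined to a secondary analysis. Per-subject accuracy, the primary result, is unaffected, and the article ties no sample-size figure to this model. Correcting it will not make the on/off contrast a pure medication effect: the on state is always the first visit, so no model for these data separates medication from visit order.

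**What to change.** Replace the model sentence in Secondary Outcomes with:

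> Accuracy, sensitivity and specificity, computed per patient, task and medication state, will each be analysed with a mixed model with fixed effects for task (ST, DCT, DMT), medication state (on/off) and their interaction, and random effects for patient, patient-by-medication and patient-by-task; contrasts will be reported with 95% CIs.

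Add three short provisions:

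- If window counts are modelled as binomial instead, allow for the 80% overlap with an overdispersion term, a cell-level random effect or a bootstrap by patient.
- Report how many patient-by-condition cells contain no freezing windows, since these carry no information on sensitivity under any model.
- State that the on/off contrast is confounded with visit order, and interpret it accordingly.

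The cost is a few lines of text. No data collection, patient burden or sample size changes, and the article places analysis after all data are gathered, so the correction can be made before any results are seen.
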